## Treatment of Subjects and Investigational Equipment

Prior to the start of the study all health care providers involved in delivery room care will be trained in using the Concord for PBCC. A standard operating procedure has been developed to optimize close collaboration between neonatologist and obstetrician. All neonatal caregivers involved are trained and accredited for neonatal resuscitation. Centers will adhere to local resuscitation guidelines for stabilization.

### Intervention

Preterm infants randomized to the intervention group will be stabilized according to PBCC. With the exception that the infant is stabilized close to the mother and the cord is clamped at a later stage, the infant will receive standard postnatal respiratory management and heat loss prevention.

#### Physiological-Based Cord Clamping

The Concord will be placed next to the bed of the mother and all equipment will be checked before the second stage of labor has started or prior to cesarean section. Stabilization will be started as soon as the infant is placed on the platform and according to the local resuscitation guidelines.

When an infant is randomized to PBCC, the standard resuscitation table will also be set and prepared for use. In any case if the attending neonatologist and/or obstetrician decides that PBCC should not be performed or interrupted, the infant can be taken to the standard resuscitation table for (further) stabilization.

##### Timing of cord clamping, performing PBCC

Stabilization of the infant is performed while the cord is intact and the cord will be clamped after the infant is respiratory stable, defined as the establishment of regular spontaneous breathing, a heart rate >100 bpm and oxygen saturation above 90% while using supplemental oxygen < 40%.

##### Summary of standard operating procedure PBCC

The Concord is placed next to the bed of the mother, preferably at the left side.After the infant is born, the obstetrician holds the baby.The platform of the table is placed as close as possible to the mother's pelvis to make sure that stretching of the umbilical cord will not occur.The infant is placed on the platform and receives stabilization and heat loss prevention according to standard guidelines. The nurse places the oximeter sensor on the right wrist of the baby.In case of vaginal delivery, the mother is able to touch and stimulate the infant during stabilization. The nurse communicates with the parents to explain the progress and procedures.The cord is clamped as soon as the infant is respiratory stable, as defined before.To ensure optimal placental transfusion the minimum clamping time is 3 min.If the infant does not reach the criteria for being stable, the maximum clamping time is 10 min.After clamping, the platform will be withdrawn and placed next to the bed of the mother.Uterotonic drugs are administered immediately after cord clamping.The infant will be prepared and transferred to the transport incubator.

In case of twins and vaginal delivery, the same definition of the moment of cord clamping will be used. Clamping in the first infant will be performed sooner if the second infant of the twins is about to be born. The first infant will then be transferred to the standard resuscitation table, so that the second twin can be stabilized on the Concord.

PBCC can be aborted at any time during the procedure. The cord will be clamped and the infant is transferred to the standard resuscitation table:
When an emergency occurs with mother or second twin and more working space is necessary for the obstetrician.When full resuscitation is needed and the parents have expressed this should not be performed close in their view.When maternal blood loss is excessive and the obstetrician decides to clamp the cord and to administer uterotonic drugs immediately.

These infants remain included in the study, as this is an outcome parameter.

### Standard Treatment

Preterm infants are clamped first and then transferred to the standard resuscitation table for further treatment and intervention needed for cardiopulmonary stabilization, according to the local resuscitation guidelines. Clamping is time based and performed immediately or delayed at 30–60 s, depending on the clinical condition of the infant. Uterotonic drugs are administered immediately after cord clamping.

### Investigational Equipment

The Concord is specially designed to provide full standard care in stabilization of preterm infants at birth while the cord remains intact. Via an extendable arm, the support platform can be placed very close to the mother so that a preterm infant, independent of the length of the umbilical cord, can receive PBCC. A patented slit is incorporated in the working plate in which the umbilical cord can be placed, thereby preventing stretch of the umbilical cord. All equipment that is needed for stabilization and resuscitation is incorporated in the table.

For standard care a routine resuscitation table is used. This table is normally situated in the resuscitation room next to the delivery room.

Both tables are provided with standard equipment for stabilization and resuscitation:
T-piece ventilatorRadiant heaterSuctioning deviceOxygen blenderHeater and humidifierHeated resuscitation circuitPulse oximeter

Both tables have a respiratory function monitor built in. The monitor depicts respiratory function, the applied respiratory support, oxygen saturation, heart rate, FiO2, and a video connected to an MRT-A RFM (Applied Biosignals, Weener, Germany).

## Procedures

### Recruitment and Consent

Parental written informed consent will be obtained before birth. Parents of an eligible infant will be informed by the attending obstetrician or neonatologist and asked for their consent after they have read the information letter.

### Randomization, Blinding and Treatment Allocation

Allocation will be stratified by gestational age (24–27+6 and 28–31+6 weeks) and by treatment center using variable block (4–8) sizes. Concealment of allocation will be ensured by using the randomization process of Castor EDC, an electronic data capture system. The neonatal consultant in charge of the procedure will randomize using Castor EDC. Blinding of the study is not possible.

In case of twin vaginal delivery, both infants will be randomized to the same group. In case of a cesarean section for twins, it is technically not possible to perform PBCC for both infants. After consent, both infants will be included; the first infant will receive standard treatment and the second infant will be randomized to either PBCC or standard treatment.

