## Study Design and Population

### Study Design

Randomized controlled non-inferiority study in three centers (Leiden University Medical Center, Erasmus MC University Medical Center and Amsterdam University Medical Centers). The study will be performed in the delivery room or operating room in case of a cesarean section. Infants will be randomized to either stabilization according to PBCC using the Concord (Figure 2), or according to the standard approach using the standard resuscitation table (Figure 3). The study is approved by the LUMC Institutional Review Board (IRB, P18.025) and is registered in the Netherlands Trial Register (NTR7194).

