### Study Population

Infants born prior to 32 weeks of gestational age in one of the three centers may be included in the study. Vaginally and cesarean delivered infants may be included.

Exclusion criteria are significant congenital malformations influencing cardiopulmonary transition, signs of placental abruption or placenta praevia and signs of severe fetal distress necessitating an emergency cesarean section.

Baseline characteristics will be recorded, including gestational age, birth weight, sex, and single or twin deliveries.

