### Statistical Analysis

Normally distributed data will be presented as means ± standard deviations, not-normally distributed data as medians and interquartile ranges. Categorical data will be analyzed using the Chi-square test. Continuous data will be analyzed using the Student's *t*-test or Mann-Whitney test as appropriate. Intention-to-treat analysis and per-protocol analysis will be performed. The effect of PBCC on the primary outcome will be assessed by multi-variable logistic regression analysis including possible confounders.

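### Allocation is stratified by gestational age and centre, but no stated analysis gives a difference in seconds adjusted for them, which costs a few points of power

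*Protocol article*

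**What the plan says.** The section Randomization, Blinding and Treatment Allocation states: "Allocation will be stratified by gestational age", in two bands (24 to 27+6 and 28 to 31+6 weeks), and also by centre, with block sizes varying from 4 to 8. The Study Design section gives the number of sites: "Randomized controlled non-inferiority study in three centers". Two gestational-age bands in three centres make six strata.

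The Statistical Analysis section names general tests by type of data. For categorical data: "Categorical data will be analyzed using the Chi-square test". For continuous data it names the Student's t-test or the "Mann-Whitney test as appropriate". It then has one sentence specific to the primary outcome: "The effect of PBCC on the primary outcome will be assessed by multi-variable logistic regression analysis including possible confounders".

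Under Primary Outcome, the endpoint is a time measured from birth. Under Sample Size Calculation, non-inferiority is judged by the lower limit of a two-sided 95% confidence interval for the difference in mean time (standard minus PBCC) against −75 s.

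The covariates needed are available. Under Study Population: "Baseline characteristics will be recorded, including gestational age, birth weight, sex, and single or twin deliveries". Centre is known from the randomisation.

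**The concern.** Stratified allocation balances the strata between the arms, so differences between strata drop out of the treatment contrast. A plain t-test still counts those differences in its standard error. If the strata predict the outcome, the reported interval is too wide. That they do is plausible but not documented: gestational age was chosen as a stratifier, and the centres follow local resuscitation guidelines.

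The planned adjusted model does not close the gap. Logistic regression needs a binary outcome and returns an odds ratio. Whatever covariates it holds, it gives no difference in seconds and no limit to compare with −75 s. Of the methods named, only the unadjusted t-test addresses the quantity on which the trial is sized.

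At stake is the chance of showing non-inferiority when it is true. An interval that is wider than necessary makes it harder to clear the limit, and this trial has no power to spare.

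**Working it through.** **Inputs.** From Sample Size Calculation: SD 2 min = 120 s, limit 75 s, true difference 0, one-sided 2.5%, 80% power, 32 per arm. The share of variance explained by gestational age and centre (R²) is not in the document. I assume 0.05 to 0.30.

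**1. The plan's own figure.**

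n per arm = 2 × SD² × (z₀.₉₇₅ + z₀.₈₀)² / limit² = 2 × 120² × (1.960 + 0.842)² / 75² = 40.2, rounded up to 41, or 82 in total.

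The stated 64 is not reproduced. It is obtained with one-sided 5%: 2 × 120² × (1.645 + 0.842)² / 75² = 31.7, rounded up to 32 per arm.

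With 32 per arm, the standard error is 120 × √(2/32) = 30 s. Power at one-sided 2.5% is Φ(75/30 − 1.960) = Φ(0.54) = 70.5%, or 69.2% with the noncentral t distribution on 62 degrees of freedom.

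**2. Adjusted analysis.** Residual SD = 120 × √(1 − R²), and the standard error is a quarter of that. Gestational age takes one degree of freedom and centre two, so 62 becomes 59. Power comes from the noncentral t distribution with noncentrality 75/SE. Example at R² = 0.20: residual SD 107.3 s, SE 26.8 s, noncentrality 2.80, power 78.5%.

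**3. Unadjusted t-test on the same stratified allocation.** The true SE is the one in step 2, because the strata are balanced, but the test still uses about 30 s. The normal approximation is Φ((75 − 1.960 × 30) / true SE). At R² = 0.20 this is Φ(16.2/26.8) = 72.7%. The table gives t-test values from simulation with balanced strata (400,000 trials per row), which run one to two points lower. The actual one-sided error is 1 − Φ(1.960 × 120 / residual SD).

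| R² (assumed) | Residual SD (s) | Adjusted CI half-width (s) | Unadjusted power | Adjusted power | Gain (points) | Actual one-sided error, unadjusted |
|---|---|---|---|---|---|---|
| 0 | 120.0 | 60.0 | 69.2% | 69.1% | −0.1 | 2.5% |
| 0.05 | 117.0 | 58.5 | 69.7% | 71.3% | about 2 | 2.2% |
| 0.10 | 113.8 | 56.9 | 70.1% | 73.6% | about 3.5 | 1.9% |
| 0.20 | 107.3 | 53.7 | 71.1% | 78.5% | about 7.5 | 1.4% |
| 0.30 | 100.4 | 50.2 | 72.3% | 83.6% | about 11 | 1.0% |

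The unadjusted half-width is about 60 s throughout.

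**4. Can adjustment alone restore 80% with 64 infants?** The residual SD would have to be 75 / (2.802 × 0.25) = 107.1 s, so R² = 1 − (107.1/120)² = 0.20. With the t distribution on 59 degrees of freedom it is about 0.23.

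These figures treat all the explained variance as balanced by the stratification. Exact gestational age may explain more than the two bands do, by an unknown amount.

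**The case against.** The strongest reply is that the t-test and Mann-Whitney are listed as general tools, while the only sentence about the primary outcome plans an adjusted model. Its covariates, described as "including possible confounders", neither name nor exclude gestational age and centre. An article commonly leaves the list to the full protocol or the analysis plan, which are not shown. This stands as far as the list goes: unnamed covariates are not an error here. It does not rescue the model. Naming the covariates elsewhere would not turn a logistic regression into an adjusted difference in seconds.

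A reader might infer four stronger things that the document does not support.

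- *That no adjusted analysis of the primary outcome is planned.* One is planned, but of a type that does not fit the endpoint.
- *That the covariates will be picked on the results.* This cannot be shown without the unseen plan.
- *That adjustment should be credited with the whole rise from 69%.* The unadjusted test also gains a little from stratified allocation, so that baseline overstates the benefit (4.4, 9.3 and 14.4 points instead of about 3.5, 7.5 and 11).
- *That ignoring the strata causes the power shortfall or makes the test invalid.* The shortfall comes from the mismatch between 64 infants and one-sided 2.5%. The unadjusted test is conservative, so ignoring the strata does not raise the risk of a false claim of non-inferiority.

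It is also fair to say that the size rests on an assumed R². If the factors explain little, the gain is small.

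**Conclusion.** The point holds as one of efficiency and of fit between design and analysis. The stated methods that suit a continuous time ignore the stratification factors, and the stated adjusted model cannot deliver the quantity compared with −75 s. With 32 per arm, SD 120 s and no true difference, adjustment is worth about 2 points of power at R² = 0.05, 3.5 at 0.10, 7.5 at 0.20 and 11 at 0.30. These R² values are assumptions. Adjustment brings 64 infants back to 80% only if R² is about 0.20 to 0.23 or more, so it cannot be relied on to make up for the sample size. The change is worth making because it costs almost nothing.

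**What to change.** Replace the logistic model with a linear regression of time to stability on arm, gestational age (continuous, in days) and centre. Make the adjusted mean difference and its 95% CI the primary result against the −75 s limit, and report the unadjusted difference as a sensitivity analysis. Drop the open-ended reference to confounders for the primary outcome.

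The cost of the model itself is a change of wording and three degrees of freedom. No new data are needed.

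Two matters must be settled for the same model:

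- The value assigned to infants who never reach stability. The article expects 7% and includes them in all analyses.
- The handling of twins. Vaginally delivered twins share an allocation, and the first twin at caesarean section is assigned standard treatment without randomisation.

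Separately, reconcile the sample size statement: with the stated inputs it should read about 82 infants (84 with the t distribution), or give the power that 64 provides, about 70%.

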### Sample Size Calculation

There is no data available concerning the effectiveness of stabilization during PBCC and comparing PBCC with standard approaches. Few studies have performed initial respiratory support before cord clamping, but all of them used predefined timing of cord clamping, varying from 30 to 120 s. Data from our feasibility study showed a median time to obtain respiratory stability of 4:23 min [IQR 3:00–5:11] when PBCC is performed.

Using the routine approach the mean time needed to stabilize an infant, starting from birth, is 5 ± 2 min (unpublished data, Leiden database). If there is truly no difference for the time needed to stabilize an infant between the standard approach and PBCC, then 64 infants (32 in each treatment arm) are required to have 80% power to assess whether the lower limit of a one-sided 97.5% confidence interval (or equivalently a 95% two-sided confidence interval) around the difference in the mean-time to stabilization (mean time in the standard group minus mean time in the experimental treatment group) will be above the non-inferiority limit of −75 s. We have chosen the non-inferiority level of 75 s, because this difference is still acceptable according to the current clinical guidelines. We will take in consideration that 7% of infants (unpublished data, Leiden database) will not reach our primary endpoint set for stabilization, because they need continuous PPV, with or without intubation. These infants will be included in all intended analyses.

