### (Serious) Adverse Events

Adverse events are defined as any undesirable experience related to PBCC occurring to a subject during the study. All adverse events observed by the researcher or the staff will be recorded and reported to the IRB.

This study population has a high risk of serious complications (so-called “context-specific serious adverse events (SAEs)”), which are inherent to their vulnerable condition and unrelated to the intervention which is under evaluation in this trial. These complications are included in the secondary outcomes of this study and are recorded in the Case Report Form. Yearly, an overview of the context-specific SAEs for each treatment arm will be presented to the IRB.

Stabilization of preterm infants with the resuscitation table as close as possible to the mother has been performed before and is considered safe. The present study uses a similar approach, using the following modifications: (1) stretching of the umbilical cord is prevented, (2) full standard care for stabilization can be provided, and (3) extended infant monitoring is included. We do not expect that PBCC poses extra risks to standard stabilization of the preterm infant. Nevertheless, we have included several “safety parameters” as secondary outcomes. The two most important safety parameters are maternal blood loss and admission temperature of the infant at the NICU.

This is a small trial where only 32 infants will be included in each group and a Data Safety Monitoring Committee will not be installed. All SAEs mentioned above will be recorded in the Case Report Form. All SAEs will be reported to the IRB. Any unforeseen SAEs that was life threatening or resulted in death and was directly related to the PBCC approach will be reported without undue delay after obtaining knowledge of the event.

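### Vaginal twins are allocated as a pair and caesarean twins may be split between arms, but the named tests treat every infant as independent, and the arm of a split-pair mother is undefined

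*Protocol article*

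**What the plan says.** Randomization, Blinding and Treatment Allocation has two twin rules. For vaginal birth, "In case of twin vaginal delivery, both infants will be randomized to the same group". For caesarean birth both infants are included after consent; the first receives standard treatment and only the second is randomised. A caesarean pair is therefore either split between the arms or entirely in the standard arm.

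Statistical Analysis names the methods. "Continuous data will be analyzed using the Student's" t-test or the Mann-Whitney test, and "Categorical data will be analyzed using the Chi-square test". It adds a logistic regression with possible confounders for the primary outcome. No pairing term or cluster adjustment is mentioned.

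Sample Size Calculation counts infants, 32 per arm, with no allowance for twins. The decision rests on whether the lower limit of a "one-sided 97.5% confidence interval (or equivalently a 95% two-sided confidence interval") for the difference in mean time to stabilisation "will be above the non-inferiority limit of −75 s".

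Short-Term Maternal Outcomes lists blood loss, postpartum haemorrhage and wound infection. (Serious) Adverse Events states: "The two most important safety parameters are maternal blood loss and admission temperature of the infant at the NICU". Neither section says whether mothers are counted once, or which arm holds the mother of a split pair.

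**The concern.** Twins share a mother, a gestational age and a delivery, so their times to stabilisation are unlikely to be uncorrelated. When both are placed in one arm by a single allocation, the pair carries less information than two unrelated infants. A two-sample test that ignores this reports too small a standard error, which moves the lower confidence limit towards a finding of non-inferiority. The Discussion makes that finding the condition for starting the large multicentre trial.

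The mother of a split caesarean pair has one blood-loss value but an infant in each arm. If her value entered both arms, it would pull the difference towards zero, which is the unhelpful direction for a safety outcome in a trial without a data safety monitoring committee.

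**Working it through.** **Inputs from the protocol article (Sample Size Calculation).** SD 2 min = 120 s; margin 75 s; true difference 0; n = 32 infants per arm; one-sided 2.5%; power 80%.

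**Inputs assumed.** The article records single or twin delivery at baseline but gives no expected twin share and no within-pair correlation ρ. I take 4 to 8 vaginal pairs among 64 infants, ρ = 0.3 to 0.7, and 1:1 randomisation of the second caesarean twin.

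**The plan's own figure.** With independent infants, n per arm = 2(SD/margin)²(z₁₋α + z₀.₈)².
- One-sided 0.025: 2 × (120/75)² × (1.960 + 0.842)² = 40.2, so 41 per arm (82 in total).
- One-sided 0.05: 31.7, so 32 per arm (64 in total).

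The stated 64 is thus not reproduced at the stated confidence level; at 32 per arm the power is 70.5%. That is a separate matter, but it leaves less power to absorb a twin effect.

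**Variance with pairs.** Let k_c be the number of same-arm pairs and k_d the number of split pairs. A same-arm pair adds 2ρSD²/n² to the variance of the difference in means; a split pair subtracts the same amount. Hence

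Var = (2SD²/n) × DE, with DE = 1 + (k_c − k_d)ρ/n.

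**Caesarean pairs.** Under 1:1 randomisation of the second twin, about half the pairs are split and half are both standard. On average k_c = k_d and their net contribution is about zero.

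**Vaginal pairs.** All are same-arm, so DE = 1 + k_c × ρ/32. The true one-sided error of the naive limit is 1 − Φ(1.96/√DE).

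| Vaginal pairs | ρ | DE | One-sided error |
|---|---|---|---|
| 4 | 0.3 | 1.0375 | 2.7% |
| 4 | 0.7 | 1.0875 | 3.0% |
| 8 | 0.3 | 1.075 | 2.9% |
| 8 | 0.5 | 1.125 | 3.2% |
| 8 | 0.7 | 1.175 | 3.5% |

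**Simulation of the allocation rule.** Naive t-test, 64 infants, 60,000 trials per scenario, the two tails averaged, ρ = 0.3 / 0.5 / 0.7:
- no twins: 2.5% throughout
- 8 caesarean pairs only: 2.5 / 2.4 / 2.4%
- 4 vaginal and 4 caesarean pairs: 2.8 / 2.8 / 3.0%
- 6 vaginal and 4 caesarean pairs: 2.8 / 3.2 / 3.2%
- 8 vaginal pairs: 3.0 / 3.2 / 3.5%

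**On the time scale.** The naive standard error is 120 × √(2/32) = 30 s and the half-width is 1.96 × 30 = 58.8 s. Multiplying by √DE gives 59.9 s at DE 1.0375 and 63.7 s at DE 1.175. The lower limit is therefore too favourable by about 1 to 5 s, against a margin of 75 s.

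**Power of a correct analysis at 32 per arm.** Φ(75/(30√DE) − 1.96) falls from 70.5% with independence to 69.0% (DE 1.0375) and 63.5% (DE 1.175).

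**Maternal outcomes, conditional on counting from infant records.** If each arm has M records and s split-pair mothers appear in both, their values cancel and the difference in means is multiplied by (M − s)/M. With M = 32 and s = 2, which is half of an assumed 4 caesarean pairs, the factor is 30/32 = 0.94. With s = 4 it is 28/32 = 0.875.

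**The case against.** A reader might infer that the confidence intervals are simply wrong and always too narrow. The document does not support that. Split pairs make a naive interval too wide, which is conservative here, and under the stated rule caesarean pairs offset one another on average. With no vaginal twins enrolled, the error stays near 2.5%. Only the vaginal pairs push in one direction.

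A reader might also infer that maternal outcomes are double-counted. No section says so. The article lists the outcomes and is silent on the unit of analysis, so the dilution shown above is a risk of that silence and not a stated method.

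It can also be said that a condensed article leaves twin handling to a fuller plan, that its tests apply as appropriate, and that the regression covariates are open. That argument has force for the maternal unit. It has less for the infant outcomes, because the article does fix its tests, and they do not match the allocation rule it also fixes.

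The size rests on an assumed twin share and correlation and is modest. This stands.

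Finally, a cluster adjustment does not cure the fact that first caesarean twins enter the standard arm without being randomised. This is correct, and it is a separate issue.

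**Conclusion.** The point holds as a mismatch between allocation and analysis. The named tests assume independent infants, while the allocation rule creates same-arm vaginal pairs and split or both-standard caesarean pairs. The expected net effect is a somewhat too narrow interval whenever vaginal twins are enrolled. Under the assumed twin numbers and correlations, the 2.5% one-sided error becomes about 2.8% to 3.5% (2.7% by formula at the lowest corner). The existence of the mismatch is certain from the text. Its size is not, because the document gives neither the twin share nor the correlation. For maternal outcomes the supported statement is narrower: the unit of analysis and the arm of a split-pair mother are undefined, and counting her in both arms would draw the blood-loss difference towards zero.

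**What to change.** Amend Statistical Analysis in two places.

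1. **Infant outcomes.** Analyse the primary and other infant outcomes with a method that allows for correlation within mother. Suitable choices are GEE or cluster-robust errors with a small-sample correction, or a mixed model with mother as random effect. Since many clusters will be single infants and none of the twin clusters exceeds two, a random-effect variance may be poorly estimated; name one method in advance. Take the non-inferiority limit from it.
2. **Maternal outcomes.** Use one record per mother, assigned by the allocation actually randomised. For caesarean twins this is the second infant's allocation.

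The cost is a few sentences. Twin status is already recorded, so no new data are needed. Intervals become slightly wider and power slightly lower when vaginal twins are enrolled. To hold the precision of 64 independent infants, the number would rise to 64 × 1.0375 = 66.4, so 67, up to 64 × 1.175 = 75.2, so 76, over the assumed range.

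### First-born caesarean twins receive standard treatment without randomisation, are included in the trial, and nothing keeps them out of the randomised comparison

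*Protocol article*

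**What the plan says.** The Study Design section describes a "Randomized controlled non-inferiority study in three centers", and Study Population states that "Vaginally and cesarean delivered infants may be included". The section Randomization, Blinding and Treatment Allocation then sets two rules for twins.

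- Vaginal birth: "In case of twin vaginal delivery, both infants will be randomized to the same group".
- Caesarean birth: "In case of a cesarean section for twins, it is technically not possible to perform PBCC for both infants". The rule that follows from this is that "both infants will be included; the first infant will receive standard treatment and the second infant will be randomized"; only for that second twin are both arms possible.

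The same section sets the stratification: "Allocation will be stratified by gestational age (24–27+6 and 28–31+6 weeks) and by treatment center using variable block (4–8) sizes". Delivery mode, plurality and birth order are not stratification factors.

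Statistical Analysis states that "Intention-to-treat analysis and per-protocol analysis will be performed" and plans a regression with unnamed possible confounders. Sample Size Calculation and the adverse events section both work with 32 infants per group. No section says how first-born caesarean twins are handled in the analysis.

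**The concern.** A first-born caesarean twin has zero probability of receiving PBCC. Intention-to-treat preserves a comparison only among infants who were randomised, so it gives no protection for these. If they are counted with the standard group, two imbalances are built in: caesarean twins are over-represented among controls, and birth order is tied to arm. Any difference in stabilisation time linked to these features would appear as part of the treatment effect.

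The trial is small, the decision rests on a 75 s margin, and the Discussion makes a large multicentre trial depend on the result. A few such pairs could therefore matter.

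**Working it through.** **Inputs from the protocol (Sample Size Calculation):** SD 120 s (5 ± 2 min), margin 75 s, one-sided 2.5%, 64 infants (32 per arm), difference defined as standard minus PBCC.

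**Assumed, because the protocol does not give them:** the number k of caesarean twin pairs among the 64 infants, and the shift d in mean stabilisation time of caesarean twins relative to other infants.

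**The plan's own figure.** n per arm = 2 × [(z₁₋α + z₀.₈₀) × SD / margin]².
- One-sided 2.5%: 2 × [(1.960 + 0.842) × 120/75]² = 40.2, so 41 per arm and 82 in total.
- One-sided 5%: 2 × [(1.645 + 0.842) × 120/75]² = 31.7, so 32 per arm and 64 in total.

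The stated 64 is thus not reproduced at the stated level. At 32 per arm and one-sided 2.5%, power is 70.5% (normal approximation) or 69.2% (t-test). This is a separate matter. It is given here only because it sets the baseline for the power figures below.

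**Step 1: arm sizes.** Each pair gives 1 + 0.5 = 1.5 expected controls and 0.5 expected PBCC infants. With the other 64 − 2k infants split 1:1:
- control n = 1.5k + (64 − 2k)/2 = 32 + k/2
- PBCC n = 32 − k/2

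**Step 2: composition.** The caesarean-twin share is 1.5k/(32 + k/2) in control and 0.5k/(32 − k/2) in PBCC. The non-randomised share of controls is k/(32 + k/2).

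| k | Control : PBCC | Non-randomised share of controls | Caesarean-twin share, control vs PBCC |
|---|---|---|---|
| 2 | 33 : 31 | 6.1% | 9.1% vs 3.2% |
| 4 | 34 : 30 | 11.8% | 17.6% vs 6.7% |
| 6 | 35 : 29 | 17.1% | 25.7% vs 10.3% |
| 8 | 36 : 28 | 22.2% | 33.3% vs 14.3% |

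**Step 3: bias and its consequences.** Bias b = d × (difference in caesarean-twin share). SE = 120 × √(1/n_control + 1/n_PBCC), which is about 30 s throughout.
- If controls are made slower, the false non-inferiority rate at a true difference of −75 s is Φ(b/SE − 1.96).
- If controls are made faster, power at a true difference of 0 is Φ((75 − b)/SE − 1.96).

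| k | d (s) | b (s) | False non-inferiority, controls slower | Power, controls faster |
|---|---|---|---|---|
| 4 | 30 | 3.3 | 3.2% | 66% |
| 4 | 60 | 6.6 | 4.1% | 62% |
| 4 | 120 | 13.2 | 6.4% | 54% |
| 8 | 30 | 5.7 | 3.8% | 63% |
| 8 | 60 | 11.4 | 5.7% | 56% |
| 8 | 120 | 22.9 | 11.4% | 41% |

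The reference values without bias are 2.5% and about 70%.

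The formula ignores the extra variance from the shift and the correlation within pairs, so it runs somewhat high. For 6 pairs it gives 4.9% (60 s) and 8.9% (120 s). Simulation gives about 4.2% to 4.6% and 6.8% to 7.4%, and about 2.3% once first-born caesarean twins are left out.

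**Step 4: unequal arms alone.** At k = 8 (36:28) power falls only from 70.5% to 69.9%.

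**The case against.** The strongest reply is that being included in the study is not the same as being analysed as a control. The protocol never says that first-born caesarean twins count in the control arm of the primary analysis. It commits to intention-to-treat, which on its usual meaning covers randomised infants, and analysis sets are often defined in a statistical analysis plan, which is not shown here. This stands in part: an unseen plan may already exclude these infants. But the protocol itself fixes both the deterministic assignment and the inclusion, counts infants per group without distinction, and adds no restriction. Followed as written, it puts them among the controls.

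A second reply is that plurality is recorded and confounder adjustment is planned. Adjustment could deal with some of the imbalance in caesarean-twin status, since second-born caesarean twins can be in either arm. It cannot deal with being the first-born caesarean twin, because no infant allocated to PBCC has that status. Birth order and delivery mode are also not named as covariates.

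A third reply is that the rule has a stated technical reason. That explains the care given, which is not questioned here. It does not justify the comparison.

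A reader might go further and infer that the trial is biased towards declaring non-inferiority, or that the departure from 32:32 materially weakens it. The documents support neither. They give no pair count and no prognostic difference, so the sign is open, and a 120 s shift is a full SD. The unequal arms cost less than one percentage point of power even at 8 pairs.

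**Conclusion.** The point holds. The protocol assigns some infants to standard treatment without randomisation, includes them, and does not keep them out of the comparison. The expected 3:1 split within caesarean pairs and the link between birth order and arm follow directly from the text and need no assumption.

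The size and direction of the bias do not follow from the text. The range of about 3 to 23 s, or 4% to 30% of the margin (3.3/75 to 22.9/75), and the 3% to 11% false non-inferiority rate rest on the assumed 4 to 8 pairs and 30 to 120 s shift. With 2 pairs the bias would be about 2 to 7 s, and with none there is no problem. It still needs correcting before analysis, because adjustment cannot fully remove the bias and its sign cannot be known in advance.

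**What to change.** State in Statistical Analysis that the primary analysis and every other comparative analysis, intention-to-treat and per-protocol alike, contain only infants whose own allocation was randomised: singletons, vaginal twins (as randomised pairs) and second-born caesarean twins. Report first-born caesarean twins descriptively and for safety only. Care of the twins does not change.

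The cost depends on how the 64 is counted, and the protocol should say which applies.
- **64 enrolled in total:** k fewer infants are analysed. With 6 pairs, 58 infants remain (29 per arm expected), and t-test power at one-sided 2.5% is about 65% instead of about 69%.
- **64 randomised infants:** 64 + k must be enrolled (68 for 4 pairs, 72 for 8), and power stays at about 69%.

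In either case the power figure should be restated for the infants actually compared.
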